## Abstract

**Background:**

The Military Health and Nutrition Examination Study (MHANES) is modeled after the National Health and Nutrition Examination Survey (NHANES). NHANES does not enroll active-duty Service Members, who are exposed to unique and adverse occupational challenges compared with civilians. Therefore, NHANES data are not generalizable to Service Members.

**Objectives:**

The objective of MHANES is to fill this gap by assessing dietary intake, cardiometabolic health, body composition, biomarkers of nutritional status and health, mental well-being, injury prevalence, genetics, gut microbiome composition, and physical performance in a representative sample of Army Soldiers.

**Methods:**

MHANES recruited Soldiers (n = 648) from Army installations across the United States. Participants attended an in-person visit to complete a 24-h dietary recall and questionnaires regarding demographics, physical and mental health, physical activity and performance, and dietary supplement and medication use. Height, weight, blood pressure, resting heart rate variability, physical activity, sleep, resting metabolic rate, hemoglobin mass, and blood volume were measured. Body composition was assessed using bioelectrical impedance, 3-dimensional body imaging, dual-energy X-ray absorptiometry, and circumference measurements. Blood and urine samples were collected to measure biomarkers of nutritional status, health, and genetics. Stool samples were collected to assess microbial diversity and composition. A second 24-h dietary recall was administered 3 to 10 d after the in-person visit.

**Conclusions:**

Data collected will be used to determine disease risk and prevalence and to investigate relationships between dietary intake, nutritional status, and markers of health and disease in Army Soldiers. Findings will guide evidence-based screening, education, intervention strategies, and policy decisions to improve Army health. Although the current study is focused exclusively on United States Army Soldiers, a long-term goal is to expand this research to other service branches and include additional sampling cycles similar to NHANES.

This trial was registered at clinicaltrials.gov as NCT06380322.

## Introduction

In 2009, the United States Department of Defense (DoD) established the Total Force Fitness framework across the Services to promote health and performance of active-duty Service Members (SMs) [1]. This framework consists of 8 domains, including physical fitness, social fitness, psychological fitness, environmental fitness, nutritional fitness, financial fitness, spiritual fitness, and medical and dental preventive fitness [1]. Using this framework, the Army implemented the Holistic Health and Fitness (H2F) system in 2020 to optimize physical and nonphysical performance and promote overall well-being in Soldiers [2]. However, nutritional status, cardiometabolic health, and behavioral determinants, such as dietary intake, physical activity, and sleep, are not well characterized in the entire Army population.

Past studies evaluating relationships between behavioral factors, nutritional status, and health and disease have largely been constrained to smaller, specialized populations (e.g., basic trainees, special forces), limiting generalizability to the broader Army. Therefore, there is a need for standardized assessment of dietary intake, nutritional status, physical activity, sleep, disease prevalence, and overall health and performance in a representative sample of Soldiers to characterize behavioral factors, assess disease prevalence, and examine associative relationships between behavioral factors and health and disease. These findings can then be used to inform H2F efforts and guide the design of interventions that investigate dietary modifications, new ration formulations, weight management strategies, and pharmacotherapies to promote health.

The current study, the Military Health and Nutrition Examination Study (MHANES), is modeled after the NHANES conducted by the Centers for Disease Control and Prevention, in collaboration with the NIH, the National Center for Health Statistics, and the USDA [3]. NHANES assesses the nutritional, biochemical, and medical status of a representative sample of the United States population. NHANES is essential for the nation’s health information system because it collects data directly from participants through clinical examinations and medical and laboratory testing, in conjunction with self-reported data. However, NHANES does not enroll active-duty SMs. Furthermore, NHANES data are not generalizable to SMs because they are often exposed to more adverse occupational challenges than the civilian population, such as long work hours, extensive physical demands, deployment, separation from family members, and austere environments. Therefore, comprehensive information on the nutritional, biochemical, and medical status of a representative sample of active-duty SMs is not currently available. MHANES is designed to address this research gap by assessing nutritional, biochemical, and medical status and lifestyle behaviors in a representative sample of active-duty Army Soldiers.

## Trial aim

The aim of MHANES is to provide comprehensive information on nutritional, biochemical, and medical status and lifestyle behaviors of active-duty Army Soldiers by assessing dietary intake, cardiometabolic health, body composition, biomarkers of nutritional status and health, mental well-being, sleep, physical activity, injury prevalence, genetics, gut microbiome composition, and physical performance in a large representative sample of Army Soldiers.

## Methods

### Institutional review board approval and trial registration

The study protocol was approved by the Institutional Review Board at Pennington Biomedical Research Center (PBRC) and the United States Army Medical Research and Development Command (USAMRDC) Office of Human Research Oversight. The clinicaltrials.gov identifier is NCT06380322.

### Study population and trial design

In this cross-sectional study, data were collected from August 2024 to February 2026 in active-duty Army Soldiers (*n* = 648) from the following 5 geographically dispersed Army installations in the United States: Fort Polk, Louisiana; Fort Campbell, Kentucky; Joint Base Lewis-McChord, Washington; Fort Carson, Colorado; Fort Stewart, Georgia (Table 1). These Army installations represent a convenience sample because selection was based on the availability of a letter of support from the Commanding General at each installation. Marketing efforts at each installation were as broad as possible to ensure adequate sampling across demographic subgroups of sex, race/ethnicity, and grade/rank and, ultimately, to recruit a representative sample of active-duty Army Soldiers. In addition, we oversampled females and certain race/ethnicity groups to ensure that these groups are adequately powered for analyses (Table 2). For example, females were oversampled because they are a smaller proportion of the Army population and are at greater risk of several nutritional deficiencies including iron and iodine [4,5].

**TABLE 1 tbl1:** Data collection location, dates, and enrollment for the Military Health and Nutrition Examination Study (MHANES) population

Location	Date	Enrollment
Fort Polk, LA	August to September 2024	126
	January to February 2026	38
Fort Campbell, KY	September to October 2024	134
Joint Base Lewis-McChord, WA	January to February 2025	137
Fort Carson, CO	March to April 2025	123
Fort Stewart, GA	July to August 2025	90

**TABLE 2 tbl2:** Oversampling plan for the Military Health and Nutrition Examination Study (MHANES) population

	Percentage of the Army population^1^	Percentage of the MHANES population^2^
Sex		
Female	16	32
Male	84	68
Race/ethnicity		
American Indian or Alaskan	2	4
Native/other/unknown		
Asian or Pacific Islander	7	14
Non-Hispanic Black	21	21
Hispanic	17	17
Non-Hispanic White	53	44
Rank		
Enlisted	82	82
Officer	18	18

1 Based on demographics from 2021.

2 Target demographics for MHANES.

Post-stratification survey weights were applied to align the analytic sample with the demographic composition of the active-duty Army population based on sex, race/ethnicity, and rank. Although these weights do not explicitly account for site-based recruitment, they help mitigate potential bias to the extent that differences across installations are reflected in these characteristics. In addition, active-duty Soldiers routinely relocate between installations approximately every 3 to 4 y, resulting in broadly similar demographic distributions across sites. Steps to minimize sampling bias included geographic dispersion of installations, broad recruitment strategies at each site, and balanced enrollment targets across installations (∼100–150 participants at each site).

Interested Soldiers attended an in-person briefing to learn about the study and, if still interested in participating, signed the informed consent before any data collection. The study inclusion and exclusion criteria are shown in Table 3. After signing the informed consent, volunteers are asked to complete a screening questionnaire to obtain demographic information (i.e., sex, age, race/ethnicity, rank/grade, area of assignment, military occupational specialty, and duration at current duty station). Volunteers were then given instructions (i.e., no alcohol for 48 h, no exercise or caffeine for 12 h, no food or beverages except water for 10 h, and no tobacco or nicotine products in the morning before the visit) and scheduled for 1 in-person visit (∼4 h) where outcome measures were assessed (see below). A stool sample kit was provided to volunteers so they could collect the sample at home and bring it to the study visit. Volunteers were also provided with a bag to carry their dietary supplements and medications to the study visit. A subset of volunteers received an actigraph watch to monitor sleep and physical activity to wear until their in-person visit (∼4–7 d after the briefing visit).

**TABLE 3 tbl3:** Inclusion and exclusion criteria for the Military Health and Nutrition Examination Study

Inclusion criteria	Exclusion criteria
• United States Army SMs ≥18 y • Willing to have biological samples stored for future use • Willing to have data linked to the Soldier Performance, Health, and Readiness (SPHERE) database	• Inability to understand verbal or written instructions in English • SMs relocating or getting out of the Army in the next 30 d • Pregnant • Currently in Basic Combat Training(BCT) and/or One-station Unit Training (OSUT)

Abbreviation: SM, Service Member.

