#### Anthropometrics

Body weight was assessed in the morning (06:30–11:00), after an overnight fast, after first toilet use, and in light clothing using a bioelectrical impedance device (InBody 770; InBody USA). Height was measured in duplicate to the nearest 0.1 cm using a stadiometer (Seca; Creative Health Products).

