#### Twenty-four hour dietary recall assessment

Twenty-four hour dietary recalls were collected using Automated Self-Administered 24-Hour Dietary Recall (ASA24) (https://epi.grants.cancer.gov/asa24/), providing estimates of macronutrient (protein, carbohydrate, and fat) and micronutrient (vitamins and minerals) intake. ASA24 is a validated and standardized web-based tool that assesses food, beverage, and dietary supplement consumption in the previous 24 h. ASA24 is automated and self-administered and allows individuals to record what food and dietary supplements they consumed without the assistance of an interviewer, thereby minimizing respondent bias. This study collected one ASA24 dietary recall at the in-person visit and a second 24-h dietary recall 3 to 10 d later electronically via a personal device.

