### Statistical analyses

Statistical procedures will include the following: *1*) means, SEs, and distributions will be calculated for the entire sample for each variable; *2*) differences in means by sex, age, race/ethnicity, and rank will be computed and assessed with analysis of variance for statistical significance; *3*) percentages of SMs above, within, and below recognized cutoff levels will be calculated for laboratory values and dietary intake of vitamins and minerals, as defined by the DRIs and MDRIs; *4*) univariable and multivariable linear and logistic regression modeling of the associations between independent variables such as laboratory variables of nutritional status and outcomes such as cardiometabolic risk factors. The data will be analyzed using R and SAS 9.4 and will apply survey weights. In addition, actigraphy data will be processed and analyzed using the accelerometry-specific GGIR package for R (version 4.3.3). As new statistical methods emerge (e.g., machine learning), these methods may be applied to the dataset.

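### The first 24-h dietary recall covers a day on which the study itself ruled out alcohol and restricted caffeine and food, and the plan does not separate it from the unrestricted second recall

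*Protocol article*

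**What the plan says.** Under Study population and trial design, the protocol article lists the instructions given before the visit: "no alcohol for 48 h, no exercise or caffeine for 12 h, no food or beverages except water for 10 h". Volunteers were then "scheduled for 1 in-person visit (∼4 h) where outcome measures were assessed".

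Under Twenty-four hour dietary recall assessment, it says that the ASA24 tool "assesses food, beverage, and dietary supplement consumption in the previous 24 h". On timing it says: "This study collected one ASA24 dietary recall at the in-person visit and a second 24-h dietary recall 3 to 10 d later", the second being completed remotely on the participant's own device. The outputs named there are macronutrients and micronutrients. Alcohol and caffeine are not named.

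Under Statistical analyses, the plan is that "means, SEs, and distributions will be calculated for the entire sample for each variable". Percentages of Soldiers relative to the DRI and MDRI cutoffs follow, for vitamin and mineral intake. Neither section mentions that the pre-visit instructions fall inside the first recall, and neither says how the two recalls enter an intake estimate.

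**The concern.** A 24-h recall is used to learn what people ordinarily eat and drink. Recall 1 asks about a day on which every participant had been told to behave differently. Recall 2 asks about a day with no stated instruction. A difference in mean intake between the two is therefore expected for any item that the instructions touch, and sampling more Soldiers does not shrink it.

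Dietary intake is among the main objectives, and associations of diet with health markers are planned. An intake estimate that draws on both recalls without separating them would mix an altered day with an ordinary one. Anyone without a second recall would contribute only the altered day. Elsewhere, the article explains that the vigilance test and the mood scale were completed fasted so as to limit acute effects of food, caffeine and nicotine. It does not consider what the same preparation does to the recall.

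**Working it through.** The plan gives no figure for this effect, so there is none to reproduce. The check is how far each restriction overlaps the recall window, and what follows for the intake estimate.

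**Inputs**
- Restrictions before visit start: alcohol 48 h, caffeine 12 h, food and drink other than water 10 h (Study population and trial design).
- Recall window: the previous 24 h, with recall 1 at the visit (Twenty-four hour dietary recall assessment).
- Visit length: about 4 h. The point in the visit at which the recall was done is not stated.
- Clock time: "Body weight was assessed in the morning (06:30–11:00), after an overnight fast" (Anthropometrics). This is the time of weighing, used here as a proxy for visit start.

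**Reading (a): the literal previous 24 h.** Let the recall be done r hours after visit start, with r from 0 to 4. The window runs from r − 24 to r, and a restriction of b hours runs from −b to 0. The overlap is min(b, 24 − r).
- Alcohol: min(48, 24 − r) = 24 h at r = 0 (100%) and 20 h at r = 4 (20/24 = 83%). The remaining r hours are spent at the visit itself.
- Caffeine: 12 h at any r in this range (12/24 = 50%).
- Food and drink: 10 h at any r in this range (10/24 = 42%).

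**Reading (b): the prior calendar day (an assumption, as a sensitivity check).** With visit start at v hours after midnight, the overlap is min(24, b − v), or 0 if that is negative.

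| Restriction | v = 6.5 (06:30) | v = 11 (11:00) |
|---|---|---|
| Alcohol, 48 h | 24 h (100%) | 24 h (100%) |
| Caffeine, 12 h | 5.5 h (23%) | 1 h (4%) |
| Food and drink, 10 h | 3.5 h (15%) | 0 h (0%) |

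These are shares of clock time, not shares of intake.

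**Consequence for alcohol.** Under either reading, the whole pre-visit part of the window lies inside the alcohol restriction. Let A be mean alcohol intake on an unrestricted day, and assume full compliance.
- Recall 1 alone: 0 against A, a shortfall of 100%.
- Simple mean of the two days (assumption): (0 + A)/2 = A/2, a shortfall of 50%.
- If the instructions remove only a fraction c of usual alcohol, the two shortfalls become c and c/2.

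The same proportions apply to the energy that alcohol supplies.

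**Consequence for other intake.** A net shortfall s on recall 1 becomes s/2 in a simple two-day mean. The document gives nothing from which to set s for energy from food, protein, carbohydrate, fat, vitamins or minerals. It could be close to zero: much of the 10-h fast is sleep, and food eaten earlier in the evening is still inside the recall window.

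**The case against.** The best defence has three parts.

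**The article does not call the recalls equivalent.** It does not say that they are averaged or pooled, and an article can leave the modelling of repeat recalls to a fuller plan. This stands, and a reader should not infer a stated decision to treat the days as interchangeable. It does not dispose of the point, because the article itself fixes the two procedures that create the difference: the instructions and the timing of recall 1.

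**The clearest effect is on items not named as recall outputs.** Macro- and micronutrients are named, and the Lifestyle and Health Questionnaire already covers alcohol use. This also stands, and it limits the point. Even so, the tool records beverages, and alcohol contributes to energy intake.

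**The effect on the named nutrients is not shown.** A reader might infer from the 42% overlap that recall 1 misses a large part of the day's food. The document does not support that. The fast is largely overnight, hours are not intake, food moved earlier is not lost, and on the calendar-day reading the fast covers only 0% to 15% of the window. The clock times also rest on when weight was taken, not on a stated visit start.

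There is a fair objection to the remedy as well. Recall 2 is remote, is compensated separately, and has no stated completion rate. Recall 1 minus recall 2 therefore also reflects setting and order, and those who complete recall 2 may be a selected group. For that reason recall 2 should not become the standard for every dietary analysis.

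**Conclusion.** The point holds in a limited form. The stated procedures place recall 1 on a day altered by the study, recall 2 has no stated restriction, and the article does not distinguish them.

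- **Alcohol and its energy:** firm. Among compliers the shortfall is 100% from recall 1 alone, and 50% under a simple two-day mean. Both figures assume full compliance and that recall 2 reflects ordinary drinking. The 50% also assumes averaging, which the article does not state.
- **Caffeine:** the direction is clear, since a restriction falls inside the window under both readings (4% to 50% of its hours). The size is unknown.
- **Food, macronutrients, vitamins and minerals:** late-evening intake may be reduced, but the effect cannot be sized and may be small. The documents do not support a general claim that nutrient intake from recall 1 is materially biased.

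The point does not invalidate the dietary data. It should be dealt with in the analysis before intake results are reported.

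**What to change.** Collection ran to February 2026, so only the analysis can change.

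1. Include a recall-number term (1 versus 2) in dietary intake models.
2. Report the paired recall 1 minus recall 2 difference in energy, alcohol and caffeine, noting that it also reflects setting and order.
3. Take any alcohol or caffeine estimate from recall 2, not recall 1. For alcohol, use the Lifestyle and Health Questionnaire as well.
4. Give a sensitivity analysis from recall 2 for the percentages below or above the DRI and MDRI cutoffs.

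The cost is analysis code and some reporting space. The estimates that rest on recall 2 will be less precise and open to selection, because only those who completed it contribute. Stating the number of completers beside those estimates would let readers judge this.

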### Outcome measures

Study personnel were trained to collect data in accordance with standardized protocols to ensure consistency and accuracy across the study.

#### Anthropometrics

Body weight was assessed in the morning (06:30–11:00), after an overnight fast, after first toilet use, and in light clothing using a bioelectrical impedance device (InBody 770; InBody USA). Height was measured in duplicate to the nearest 0.1 cm using a stadiometer (Seca; Creative Health Products).

#### Body circumferences

Neck, waist (iliac crest), and hip circumference were measured using a nonstretchable tape measure (Gullick II Tape; Creative Health Products) based on the NHANES anthropometry and Army Regulation AR600-9 methods [6,7]. Circumference measurements were taken 3 times and recorded to the nearest 0.1 cm. If the measurements were within 1 cm of each other, the mean was taken. If any 1 of the 3 measurements differed by >1 cm, an additional measurement was taken. Then, the 3 closest measures were averaged.

#### Body circumferences and composition using 2D/3D body imaging

Body circumferences and composition were also estimated using an optical imaging system (Mobile Fit Booth; Size Stream LLC). The participant stood on a stationary platform while 1 image was taken in each of 2 positions (facing the camera and a side view) using a tablet camera. The proprietary software derived circumference measurements from a 3-dimensional avatar of the participant.

#### Body composition using bioelectrical impedance

Fat mass, body fat percentage, fat-free mass, skeletal muscle mass, and total body water were measured using bioelectrical impedance (InBody 770; InBody USA).

#### Body composition measured using dual-energy X-ray absorptiometry

At installation(s) with an accessible dual-energy X-ray absorptiometry (DXA) machine (i.e., Fort Stewart), all participants (*n* = 90) were asked to undergo a DXA scan. Body composition (total body weight, fat-free mass, fat mass, and bone mass) was determined after an overnight fast (Lunar Prodigy; General Electric). A pregnancy test was administered to all females before the DXA scan to confirm that they were not pregnant.

#### Heart rate variability

Resting heart rate variability (HRV) was examined according to the Task Force for Pacing and Electrophysiology guidelines [8]. Heart rate variations were recorded with the Zephyr Bioharness (Zephyr Technology Corporation), a wireless chest-worn device that allows heart rate, respiratory rate, core temperature, activity levels, and posture to be recorded in real time. Volunteers were asked to lie in a supine position and remain motionless and awake for ∼20 min in a quiet area while wearing the Zephyr Bioharness. Resting HRV with spontaneous breathing was collected from minutes 05:00 to 12:00. Participants were then asked to breathe at an inhalation:exhalation rate of 5 s:5 s by following an audible metronome, and resting HRV with paced breathing was collected from minutes 13:00 to 20:00. Time- and frequency-domain and nonlinear components of HRV will be calculated and analyzed using Kubios software (available at http://kubios.uef.fi) [9].

